Prior to the start of the study, a dental hygienist will perform teeth surface cleaning to remove plaque in both groups of participants, and provide brushing instructions. Participants will be made to watch video teaching materials, to ensure homogeneity in the instructions given. After that, the intervention group will install a digital device (GUMPLAY^®^) linked with a mobile application onto the bottom of a toothbrush and perform teeth brushing under guidance of the application. This device: (1) enables visualization of the toothbrush position and provides a guide for the brushing sequence during teeth brushing, (2) ensures the brushing time lasts for at least 3 minutes, and (3) enables the user to visualize whether he or she is moving the toothbrush in small steps. The control group will install the digital device (GUMPLAY^®^), that functions only to collect brushing logs, to the bottom of a toothbrush and perform regular teeth brushing without using the mobile application. Both groups of participants will use a standard toothpaste (Ora^2^ me STAIN CLEAR, Sunstar Inc., Osaka, Japan) and toothbrush (GUM dental brush #166M, Sunstar Inc., Osaka, Japan).

1. Method of randomization

For the randomization process, the stratified permuted block randomization method will be used, where participants are stratified by gender (male / female) and baseline PCR score (≥60% / below 60%). Randomization codes in each stratum will be prepared in advance, and those participants that meet the study participation criteria based on the baseline measurement results shall be assigned to one of the two groups.

1. Blinding method

The participants will not be blinded (open-label), while randomization concealment for the group will be maintained for the dental hygienist who performs 3 oral examinations, and the data analyst.

1. Test items

- Baseline data
- PCR score
- Outcome data and measurement timing
- PCR score (week 2 and week 4)
- Teeth brushing speed and amplitude (the target is week 4/some participants: 10 participants in each group) during brushing.
- Patient background information

Age, gender, date of birth, profession, history of dental clinic visits, status of use of interdental cleaning instrument, and status of oral disease.

- Information on teeth brushing
- Frequency of teeth brushing in one day (obtained from GUMPLAY^®^)
- Teeth brushing time (obtained from GUMPLAY^®^)
- Daily teeth brushing record (obtained using a
- questionnaire)
- Questionnaire

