- In the past month, have you been conscious of brushing each tooth surface?
- In the past month, have you been conscious of moving the toothbrush in small steps?
- In the past month, for how many minutes have you been brushing each time?
- In the past month, have you been in the habit of doing something else while slowly brushing your teeth, and not focussing on just the teeth brushing?
- In the past month, how often have you been brushing your teeth regularly in a day?
- Compared to before the study, are you confident about the level of cleanliness of the inside of your mouth?
- Compared to before the study, are you confident about the way you brush your teeth?
- In the past month, have you felt that teeth brushing is bothersome?
- Do you presently have any concerns about the inside of your mouth?
- Are you currently interested in oral health?
- During the study period, did you visit a dental clinic?
- During the study period did you administer an antibiotic?

1. Schedule

[figure not shown]

Group using the GUMPLAY^®^ linked to a mobile application

Study duration: 4 weeks

Second examination

Third examination

Group not using the GUMPLAY^®^ linked to a mobile application

Random assignment of participants

First examination

Enrollment to participate into the study

2 weeks

2 weeks

1. Summary of the analysis

- Primary outcome:
- PCR score at week 4 (using the 6-point method: evaluation of 6 parts of each tooth; the participants analyzed will be the Full Analysis Set)
- Secondary outcomes:
- PCR score at week 4 (using the 6-point method: evaluation of 6 parts of each tooth; the participants analyzed will be the Per Protocol Set)
- PCR score at week 2 (using the 6-point method: evaluation of 6 parts of each tooth)
- PCR score (using the 4-point method: evaluation of 4 parts of each tooth)
- Brushing time in one day
- Frequency of brushing in one day
- Method of evaluation: The PCR score will be evaluated by three dental hygienists using plaque staining fluid. The same dental hygienist will perform the baseline and outcome measurements of the same participant. In addition, to minimize inter-evaluator differences, the dental hygienists will be educated in advance, and calibration will be performed. Brushing speed and amplitude will be measured for some participants who give their consent to do so. For the measurements, brushing will be performed using a specialized toothbrush connected to a measuring device using a code.

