- Method of analysis: The analysis will consist of two entities, a Full Analysis Set (FAS) and a Per Protocol Set (PPS).
- FAS

The analysis set of the primary and secondary outcomes. For the respective items, the mean value of the change from baseline in the intervention and control groups will be compared based on an intention-to-treat analysis. The estimated value of the difference between the 2 groups (intervention group－control group) and the 95% confidence intervals will be calculated. The p-values of the t-test will calculate the null hypothesis that the true intergroup difference is not different from zero. The significance level of the test will be 5%. A stratified analysis will be performed using the patients’ background information (e.g. frequency of brushing in one day).

- PPS

The analysis set of the secondary outcome. An individual to whom one or more of the following conditions apply will be excluded from the FAS:

1. A participant who visited a dental clinic during the study period.
2. A participant who administered an antibiotic during the study period.
3. A participant in the intervention group whose 4-week history of using GUMPLAY® did not show the at least once daily usage for more than 5 days　(GUMPLAY® was not switched on).
4. A participant in the control group whose 4-week history of using GUMPLAY® (one that functions only to collect brushing log) did not show the at least once daily usage for more than 5 days　(GUMPLAY® was not switched on).

The same analysis performed for the FAS will be performed for the PPS.

1. **Study period**
2. Participant enrollment period: Twelve months after obtaining the approval of the ethics committee, until the required number of participants is reached.
3. Participant observation period: Thirteen months (4 weeks after enrollment into the study) after obtaining the approval of the ethics committee
4. Study period: Thirty-six months from the date approval is received from the ethics committee.
5. **Informed consent**
6. Acquisition of new samples and information to conduct the study

In this study, a non-invasive intervention will be performed and, to conduct the study using newly acquired samples and information, the informed consent of the participants will be obtained after providing them with a written explanation.

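### Change from baseline is prescribed for brushing time and brushing frequency, but both are sourced from a device for which no reading before allocation is described

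*Protocol*

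**What the plan says.** - Protocol, Summary of the analysis, Method of analysis, FAS: this set serves the primary and secondary outcomes, and "For the respective items, the mean value of the change from baseline in the intervention and control groups will be compared". The between-group difference, its 95% confidence interval and a t-test follow. No outcome is exempted.
- Protocol, Summary of the analysis, Secondary outcomes: five items. Three are PCR scores; the other two are "Brushing time in one day" and "Frequency of brushing in one day". No source or time window is attached to these two.
- Protocol, Test items, Information on teeth brushing: the source is given as "Frequency of teeth brushing in one day (obtained from GUMPLAY" and "Teeth brushing time (obtained from GUMPLAY". A daily brushing record by questionnaire is listed beside them.
- Protocol, Test items: under "Baseline data" the item that follows is the PCR score.
- Protocol, Intervention methods: the device appears only as part of what each group does. It is linked to the application in the intervention group and used as a logger in the control group.
- Protocol, Registration procedure and questionnaires: a pre-study questionnaire is collected before registration. It asks for minutes per brushing and usual brushings per day. Both groups answer the same two questions for the past month at the end.

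**The concern.** A change score needs the same quantity measured before allocation. For PCR this holds. For brushing time and frequency, the source named in the protocol produces data only once a participant is using the allocated version of the device, after cleaning and instruction. Early device readings cannot serve as baseline, because they already follow allocation.

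Whoever carries out the stated analysis must therefore choose among device follow-up minus questionnaire baseline, questionnaire at both times, or device follow-up alone. The protocol prescribes a change score without saying which. The first option invites a reader to take an instrument difference for a change in behaviour. The second replaces a logged measure by recall from participants who know their group. The choice could also be made after the data are seen.

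**Working it through.** **Tracing source and timing**

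| Quantity | Before randomization | During the 4 weeks | At the end |
|---|---|---|---|
| PCR score | examined | week 2 | week 4 |
| Brushing time, device | none described | logged in both groups | – |
| Brushing frequency, device | none described | logged in both groups | – |
| Brushing time, questionnaire | minutes per brushing | daily record listed, content not given | minutes per brushing, past month |
| Brushing frequency, questionnaire | times per day | daily record listed, content not given | times per day, past month |

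The FAS rule fits the PCR row and the two questionnaire rows. It does not fit the two device rows, which are the source that Test items assigns to these outcomes. The questionnaire also asks for minutes per brushing whereas the outcome is time per day, so a subtraction would first need the product of minutes and times per day.

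**Is a mixed change score biased between arms?** Let D be the device value during follow-up and S the self-report before randomization.

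- Expected difference in change = [E(D, intervention) − E(S, intervention)] − [E(D, control) − E(S, control)].
- Randomization makes E(S) equal in the two arms, so this reduces to E(D, intervention) − E(D, control). The contrast is unbiased.
- Within one arm, E(D) − E(S) is the behaviour change plus the average gap between device and self-report. The two parts cannot be separated.

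**What does subtraction cost in precision?** The protocol gives no SDs or correlations for these measures, so the following are assumptions. Let rho be the correlation between D and S, and let both have the same SD, sigma.

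- Variance of change: 2·sigma²·(1 − rho).
- Residual variance after adjusting D for S: sigma²·(1 − rho²).
- Ratio: 2(1 − rho)/(1 − rho²) = 2/(1 + rho).

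| Assumed rho | Ratio | Equivalent of 85 per group: 85·(1 + rho)/2 |
|---|---|---|
| 0.2 | 2/1.2 = 1.67 | 51 |
| 0.3 | 2/1.3 = 1.54 | 55 |
| 0.5 | 2/1.5 = 1.33 | 64 |

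The 85 is the protocol's number per group at 90% power before drop-out. It was derived for PCR and is used here only to give the ratio a scale.

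With unequal SDs, write k = SD(S)/SD(D). The ratio becomes (1 + k² − 2·rho·k)/(1 − rho²), which equals 1 + (k − rho)²/(1 − rho²). It is never below 1, so subtraction cannot beat adjustment, but the size of the loss depends on k as well as rho.

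Against device follow-up alone with equal SDs, the change score has variance 2(1 − rho): 1.6, 1.4 and 1.0 times at the same three correlations. At rho below 0.5, subtracting the self-report is worse than ignoring it.

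**The case against.** A reader might infer that no baseline exists for these outcomes, that the stated analysis cannot be done, or that two secondary outcomes have no valid analysis. The documents do not support any of these. The initial questionnaire precedes randomization and covers both quantities. The end-of-study questionnaires repeat both questions in both groups, so a change on one instrument can be computed. The FAS text itself cites daily brushing frequency as background information. The outcome list names no source, so self-report at both times would satisfy the analysis rule as written. Even the mixed change score gives an unbiased between-arm contrast, and the protocol tests only that contrast, not the change within an arm.

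Two further points are fair. The variance ratio is the general price of a change score against covariate adjustment and would apply to a same-instrument baseline with the same correlation, so it does not by itself show that the rule is ill-fitting. And the PCR heading under Test items comes from a list whose levels may have been lost, so little weight should rest on PCR being the only item there.

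What remains does not depend on that heading. Test items names the device as the source, and the device is described only within the allocated conditions. Using self-report throughout departs from that source and gives up what the control group's log-only device provides: the same objective measure in both arms of an open-label trial. Details of source and window are often left to an SAP, and one may exist. Here, however, the protocol does more than stay silent: it fixes one rule for every outcome, and that rule does not suit these two as sourced.

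**Conclusion.** The concern holds in a limited form. Change from baseline is prescribed for two of five secondary outcomes whose named source has no described value before allocation. A change can still be computed, and the between-arm test would not be biased by mixing sources. The harm lies in uninterpretable changes within each arm, an open choice of source, and lost precision. The variance is 1.67, 1.54 or 1.33 times that of the adjusted comparison at rho 0.2, 0.3 or 0.5. Those figures rest on assumed correlations and equal SDs; only the direction is general.

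The point should be fixed, but it is not critical. The primary outcome and the three PCR secondary outcomes have a proper baseline and are unaffected.

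**What to change.** In Summary of the analysis, Method of analysis, restrict the baseline-referenced comparison to the PCR outcomes and add a separate rule for the other two:

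- Outcome: for each participant, the mean device-recorded brushing time per day and the mean device-recorded brushings per day over the 4 weeks.
- Comparison: the between-group difference with 95% confidence interval, adjusted for the corresponding initial-questionnaire answer (minutes per brushing for time, times per day for frequency) and for the stratification factors, gender and baseline PCR category. Adjustment needs no common scale, so the minutes answer can be used as it stands.
- Supportive only: change in self-report from the initial to the end-of-study questionnaire, labelled as such. Do not report device minus self-report as a change.

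The cost is a wording change in the protocol, and in the SAP if there is one. The device logs and both questionnaires are already planned in both groups, so no further data, visits or participants are needed.

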The target number of participants in this study was calculated based on the results of a pilot study conducted by Sunstar Inc. In the pilot study, the subjects were 9 adults aged ≥18 years old who were observed for two weeks. The plaque control record (PCR; the method for determining the plaque status in the tooth cervix) was measured (A) followed by brushing instructions from a dental hygienist. One week later, PCR was re-measured (B). On the same day, GUMPLAY^®^ was supplied to the subjects and, after receiving instructions on how to use it, they performed teeth brushing with use of the application and digital device for one week, prior to a further set of PCR measurements being performed (C).

The PCR score (A-B) of the control group in this study decreased by 9.4% from baseline, while in the intervention group, the score (A-C) decreased by 16%. Thus, assuming that the use of GUMPLAY^®^ results in a 6% decrease in the PCR score, with the level of significance (α) set at 5% (two-sided level) and the detection power (1－β）at 80％, the required number of required participants in one group is 63. Once a drop-out rate of 10 % is incorporated into the model, the number of required participants in each group is estimated to be 70. In addition, if the detection power (１－β) is set at 90%, the required number of participants in each group becomes 85 and, with a drop-out rate of 10%, the required number of subjects in each group is estimated to be 95. From the above, the target number of participants in both groups was set at 190, with a minimum of 140 becoming study subjects.

1. **Study methods and basis of the scientific ethical rationale of the study**
2. Design

Randomized controlled trial

1. Methods

- Registration procedure

The Steering Committee of this study will recruit participants from Kyoto University and provide an explanation of the study to each individual wishing to participate. After the explanation is complete, participants will be allowed to provide written informed consent and complete a pre-study questionnaire, which will be collected by the Steering Committee. The collected written informed consent forms and pre-study questionnaire will be collected, and the participants will be registered into the study.

1. Intervention methods

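### The primary t-test on week-4 change in PCR is called intention-to-treat but has no stated way to include the 10% expected to drop out, and it leaves baseline and week-2 PCR unused; a baseline-adjusted repeated-measures model is better

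*Protocol*

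**What the plan says.** The protocol's Summary of the analysis names PCR at week 4 as the primary outcome and states that "the participants analyzed will be the Full Analysis Set". Under Method of analysis, FAS, it says that "the mean value of the change from baseline in the intervention and control groups will be compared based on an intention-to-treat analysis". The difference between arms and its 95% confidence interval follow, and then the test: "The p-values of the t-test will calculate the null hypothesis that the true intergroup difference is not different from zero". No covariate is named.

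The sample-size rationale works "with the level of significance (α) set at 5% (two-sided level"), "assuming that the use of GUMPLAY^®^ results in a 6% decrease in the PCR score". At 90% power it needs 85 per group, and "with a drop-out rate of 10%, the required number of subjects in each group is estimated to be 95".

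Under Test items, the outcome is scheduled as "PCR score (week 2 and week 4"). Week-2 PCR then appears among the secondary outcomes and has no stated part in the week-4 comparison. The only exclusions listed are those that lead from the FAS to the per-protocol set: "An individual to whom one or more of the following conditions apply will be excluded from the FAS".

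**The concern.** A change score to week 4 exists only for participants who have a week-4 PCR. Going from 85 to 95 is the right allowance if those who drop out add nothing to the primary test, so the sample size and the test agree with each other. The intention-to-treat label does not sit well with either.

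Two things are at stake.

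- **Bias.** Participants are not blinded, and the protocol lists the time taken by daily use of the device as a burden. Only the intervention arm brushes under the application's guidance, and its closing questionnaire asks whether brushing felt long and whether the application became tiresome. Drop-out that differs by arm and depends on progress is therefore plausible. If intervention participants who do poorly at week 2 leave more often, an observed-case t-test flatters the device.
- **Precision.** Baseline PCR is measured on everyone and is a stratification factor in the randomisation, yet the fixed test uses it only by subtraction. Week-2 PCR is scheduled for everyone and plays no part.

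**Working it through.** **1. The plan's own sample size.** Inputs from the protocol: difference 6 points, two-sided 5%, power 80% or 90%, drop-out 10%. No SD is given. Solving n = 2(1.96 + z)²SD²/6² for the SD gives 11.92 to 12.02 from n = 63 and 12.00 to 12.07 from n = 85. I take SD = 12, an assumption that is consistent with both figures but not validated by them.

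- 80% power: 2 × (1.96 + 0.842)² × 144/36 = 62.8, so 63; 63/0.9 = 70.
- 90% power: 2 × (1.96 + 1.282)² × 144/36 = 84.1, so 85; 85/0.9 = 94.4, so 95.

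All four stated numbers reproduce.

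**2. Who lacks a week-4 value.** 10% of 190 is 19, or 9.5 per arm. That leaves 85.5 per arm and 171 in all.

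**3. Standard error and power.** Further assumptions, not in the protocol: PCR SD 15 at each visit, the same correlation r of weeks 2 and 4 with baseline, and a week-2/week-4 correlation of 0.75. An SD of change of 12 then fixes r, since 144 = 2 × 225 × (1 − r) gives r = 0.68.

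- *t-test on change:* 12 × √(2/85.5) = 1.835, about 1.83.
- *Observed-case ANCOVA on baseline:* residual SD = 15 × √(1 − 0.68²) = 11.0; 11.0 × √(2/85.5) = 1.68.
- *Repeated-measures model:* the week-2/week-4 correlation given baseline is (0.75 − 0.4624)/(1 − 0.4624) = 0.535, whose square is 0.286. If all drop-outs have a week-2 value, effective n = 85.5 + 0.286 × 9.5 = 88.2, and 11.0 × √(2/88.2) = 1.66. The simulation below gave about 1.65.

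Approximate power for 6 points is Φ(6/SE − 1.96): about 90.5% for the t-test (SE 1.835), 94.6% for ANCOVA (1.68) and 95.3% for the model (1.65). Nearly all the gain is baseline adjustment. With week-2/week-4 correlations of 0.3 to 0.7 and half to all drop-outs having a week-2 value, recovering that value adds at most about 1.4 power points.

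**4. Bias.** Simulation of 4000 trials per scenario under the step-3 assumptions: 95 per arm, true effect −6, all drop-out after week 2, dependence on week-2 change from weak to strong.

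| Drop-out, control v intervention | t-test | ANCOVA | Model using week 2 |
|---|---|---|---|
| 10% v 10% | no bias | – | – |
| 8% v 12% (weak to moderate) | bias 0.24 to 0.36 | – | – |
| 5% v 15% (weak to strong) | −6.5 to −7.0 | −6.4 to −6.8 | −6.0 |

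In standard-error units, 0.36/1.83 is just under 0.2, and 0.5 to 1.0 is 0.27 to 0.55. With no true effect at 5% v 15%, P(|Z + b| > 1.96) is 5.8% for b = 0.27 and 8.5% for b = 0.55. Direct simulation gave 6.7% to 9.4%.

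**5. Where week 2 does not help.** At 5% v 15%, if half of the drop-outs leave before week 2, the model gives −6.1 to −6.4. If all do, it gives the same answer as ANCOVA, about −6.45 to −6.8.

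**6. Scale for a sensitivity analysis.** If the effect is 6 in those who stay and intervention drop-outs gain nothing, the effect in all randomised is 6 × 0.90 = 5.4 at 10% drop-out, 5.7 at 5% and 4.8 at 20%.

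**The case against.** The strongest reply is that this is a summary. FAS membership and the handling of missing week-4 values commonly belong in a statistical analysis plan, which is not at hand, and inflating for drop-out is an ordinary power allowance that does not dictate how drop-outs are analysed. That stands: the missing rule is not in itself an error.

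A reader might go further and infer that the primary analysis is confined to completers and throws away week-2 data. The protocol does not say so. It never limits the FAS to completers, a t-test can follow imputation (from week 2 among other sources), and week-2 PCR is analysed as a secondary outcome. Nor can one say that the per-protocol rules pass over drop-outs: the two conditions on four-week device use may catch some of them.

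The bias figures are also open to challenge. The protocol gives no drop-out by arm, no correlation between visits and no link between plaque and leaving. Follow-up is four weeks, and participants receive an honorarium and the device at the end. Placing all drop-out after week 2 and making it depend on week-2 change is the setting in which the model does best.

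What remains is the method that is fixed: an unadjusted t-test on change, under a label that nothing in the text supports, when data already scheduled allow a more precise analysis that is less exposed to drop-out.

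**Conclusion.** The point holds as one about the choice of primary analysis. The stated test has no route for the roughly 10% without a week-4 PCR and uses neither baseline PCR as a covariate nor week-2 PCR. The surer gain is precision, from about 1.83 to about 1.65 points, and it rests on the assumed SDs and correlations. Protection against bias is conditional: there is nothing to remove if drop-out is alike in both arms, and up to about 1 point under a marked imbalance linked to week-2 change.

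It would be wrong to conclude that the trial is underpowered, since the stated size already allows for the loss, or that the result will be biased. The model is no complete answer either. It leaves out anyone with no post-baseline PCR. It also cannot recover participants who withdraw consent, whose data the protocol orders to be erased; that is a separate tension with the intention-to-treat label. The change is worth making but is not critical.

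**What to change.** Make the primary FAS analysis a mixed model for repeated measures of PCR at weeks 2 and 4, with arm, visit, arm-by-visit interaction, baseline PCR and unstructured covariance. Include every randomised participant with at least one post-baseline PCR, and take the week-4 difference between arms, with its 95% confidence interval, as the primary estimate.

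Keep the t-test on observed week-4 change as a supportive observed-case analysis and do not label it intention-to-treat. Add one sensitivity analysis covering all drop-outs, including those with no post-baseline PCR, for example by setting missing week-4 values in the intervention arm to the control-arm mean.

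The cost is a change of wording and a little more analysis, with no new visits, measurements or participants. The drawback is that the primary estimate becomes model-based and assumes that data are missing at random given arm, baseline PCR and any observed week-2 PCR. The sensitivity analysis probes that assumption and may give a less favourable figure.

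### The primary outcome is labelled as week-4 PCR but analysed as change from baseline by a t-test without baseline PCR or the randomisation strata: valid, but conservative and less precise than it could be at no cost

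*Protocol*

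**What the plan says.** Under Summary of the analysis, the protocol gives the primary outcome as "PCR score at week 4 (using the 6-point method: evaluation of 6 parts of each tooth", in the Full Analysis Set. Under Method of analysis (FAS), it says of each listed outcome that "the mean value of the change from baseline in the intervention and control groups will be compared based on an intention-to-treat analysis". It then asks for the difference between groups with a 95% confidence interval and adds: "The p-values of the t-test will calculate the null hypothesis that the true intergroup difference is not different from zero". No covariate or stratum term is named.

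Under Method of randomization, "participants are stratified by gender (male / female) and baseline PCR score (≥60% / below 60" per cent. The second factor is therefore the baseline value of the primary outcome itself.

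The only stratification in the analysis section is this: "A stratified analysis will be performed using the patients’ background information (e.g. frequency of brushing in one day". It does not name the randomisation factors as such and is not tied to the primary p-value.

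**The concern.** Two things do not line up. The outcome is labelled as a score at one time point, while the quantity compared is a change. And the allocation is balanced on gender and baseline PCR, while the test treats it as simple randomisation and makes no use of baseline beyond subtracting it.

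Subtraction fixes the slope of week-4 PCR on baseline at 1. If the true slope is lower, the change score over-corrects and stays negatively correlated with baseline. Stratified allocation then removes part of that baseline variation from the real sampling error of the group difference, but the ordinary t-test standard error still counts it. The interval is therefore wider than it need be, and the test rejects a true null hypothesis less often than 5% of the time. What is at stake is precision that the trial has already paid for through stratification and baseline measurement, and a clear statement of the primary variable.

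**Working it through.** **Inputs from the protocol.** Difference 6 PCR points; two-sided alpha 5%; 63 per group for 80% power and 85 for 90%; 10% drop-out, giving 70 and 95; four strata (gender by baseline PCR at 60%).

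**Assumptions, because the protocol gives no figure.** SD of change 12; baseline to week-4 correlation (rho) 0.3 to 0.7; equal variances at baseline and week 4; normality; mean baseline PCR at or near 60%; blocks of 4 in the simulations.

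**Step 1: reproduce the plan.** n per group = 2 × (SD/6)² × (z₀.₉₇₅ + z_power)². With SD 12:
- 80% power: 8 × (1.960 + 0.842)² = 62.8, so 63.
- 90% power: 8 × (1.960 + 1.282)² = 84.1, so 85.
- Drop-out: 63/0.9 = 70; 85/0.9 = 94.4, so 95.

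All four figures reproduce. The pilot quantities behind them are changes (A−B and A−C), so reading 12 as the SD of change is the natural choice.

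**Step 2: interval width.** With 85 evaluable per group, the t-test standard error is 12 × √(2/85) = 1.84, and the half-width is 1.96 × 1.84 = 3.61. ANCOVA on baseline multiplies the variance by (1 + rho)/2:

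| rho | Variance ratio | ANCOVA half-width | t-test interval wider by | ANCOVA power |
|---|---|---|---|---|
| 0.3 | 0.65 | 2.91 | 24% | 98.1% |
| 0.5 | 0.75 | 3.12 | 15% | 96.4% |
| 0.7 | 0.85 | 3.33 | 8% | 94.2% |

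**Step 3: type I error and power of the planned test.** If the 60% cut lies at the baseline mean, the two baseline strata explain 2/π = 0.637 of the baseline variance. The share of the variance of change that stratified allocation removes is then f = 0.637 × (1 − rho)/2. The true standard error is 1.84 × √(1 − f), while the test goes on using 1.84. Type I error is 2 × [1 − Φ(1.96/√(1 − f))]. Power is Φ((6 − 3.61)/true standard error).

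| rho | f | True SE | Type I error | Power |
|---|---|---|---|---|
| 0.3 | 0.223 | 1.62 | 2.6% | 93% |
| 0.5 | 0.159 | 1.69 | 3.3% | 92% |
| 0.7 | 0.095 | 1.75 | 3.9% | 91% |

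These closed forms assume exact balance within strata. Simulations with 170 evaluable participants and blocks of 4 (4,000 to 6,000 trials per setting where recorded) gave type I error of 2.5–3.1%, 3.3–3.7% and 3.8–4.3% at rho 0.3, 0.5 and 0.7. ANCOVA with baseline and strata stayed near 5%. Coverage of the t-test interval was about 96–98%. Simulated power was 91–92%, 92–93% and 91% for the t-test, against 98%, 96% and 94% for ANCOVA. Both estimators averaged about −6.0 when the true effect was −6.

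**Step 4: sensitivity.** If the mean baseline lies 1.5 SD above the cut, the strata carry less information, and simulated type I error is 4.1%, 3.9% and 4.5%. If 12 were instead the SD of the week-4 score, standard power formulas that ignore the stratified allocation give the change-score test 78.7%, 90.3% and 98.8% at rho 0.3, 0.5 and 0.7, against 92.7%, 96.4% and 99.5% for ANCOVA. The direction is the same.

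**The case against.** The strongest reply is that nothing is broken, and much of it stands.

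- **One test, not two.** A reader might infer that the protocol plans two conflicting tests of the primary question. It does not. The outcome list names variables, the FAS paragraph says how they are analysed, and no t-test on raw week-4 scores appears anywhere. Under randomisation the two contrasts have the same expected value. The label is loose and needs one clarifying line.
- **No shortfall against plan.** A reader might infer that the trial is underpowered. The sample size rests on pilot changes, matches the change-score test and, on the SD that reproduces it, delivers 90% or slightly more. What is forgone is efficiency above the target.
- **The error is conservative.** The test is unbiased and cannot raise the false-positive rate above 5%.
- **Hygienist.** The protocol states that "The same dental hygienist will perform the baseline and outcome measurements of the same participant". Hygienist is not a randomisation factor, however, and the change score already removes a constant scorer offset, so omitting this term is no fault.
- **The planned stratified analysis.** Gender is among the background items, so that analysis could cover one factor. It does not mention baseline PCR and does not replace the primary test.

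It is also true that the size of the loss depends on an SD, a correlation, a baseline mean and a block size that the protocol does not give. What survives is that the protocol itself fixes an unadjusted test, so this is not a detail left to a separate analysis plan, and a better test is available from data already collected.

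**Conclusion.** The point holds as one of definition and efficiency, not of validity. The outcome label and the quantity analysed should be reconciled, and the primary test should use baseline PCR and the stratification factors.

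On the assumptions listed (SD of change 12, rho 0.3 to 0.7, mean baseline near 60%), the planned test has a type I error of about 3–4%, closer to 5% if the mean lies far from the cut. Its interval is about 8–24% wider than the ANCOVA interval. About 3–7 points of power are forgone: 3–5 by the closed forms, up to 7 in simulation. The direction is firm unless the slope of week-4 PCR on baseline is 1. The sizes are only as good as the assumed inputs. This is a should-fix improvement; the documents do not support calling the planned analysis invalid or underpowered.

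**What to change.** State one primary analysis: ANCOVA of the week-4 6-point PCR score in the Full Analysis Set on randomised group, with continuous baseline PCR, gender and baseline-PCR category (60% cut) as covariates. Report the adjusted difference, its 95% confidence interval and the two-sided p-value. Keep the t-test on change from baseline as a sensitivity analysis. Adjusting for examining hygienist is optional.

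With baseline in the model, the treatment contrast is the same whether the response is the week-4 score or the change, so this also settles the mismatch between the outcome list and the analysis paragraph. The cost is wording only: gender and baseline PCR are already recorded, and no participants, visits or measurements are added.
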